#### **Risks associated with intravenous infusion of serelaxin**

The following adverse reactions have been reported for serelaxin in the completed clinical trials, which may represent potential safety risks for this study:

- Because serelaxin has vasodilatory properties, blood pressure decreases (defined as a SBP decrease >40 mmHg or any SBP measurements of less than 100 mmHg) were reported with serelaxin in chronic heart failure (CHF) patients. Serelaxin treatment of systemic sclerosis was also associated with decreases in blood pressure generally within normal ranges. Patients should have blood pressure monitoring while receiving serelaxin and it should not be administered to patients who are at risk of developing hypotension during vasodilator therapy.
- Increases in serum creatinine have been observed in CHF subjects receiving serelaxin but were asymptomatic.
- Menometrorrhagia, which may be associated with anaemia. Based on the pharmacology of serelaxin, menorrhagia, metrorrhagia, and dysmenorrhea are not unexpected consequences

of serelaxin administration. These events did not frequently result in discontinuation, and with lower doses and/or local administration, they may not occur.

- In CHF patients, a decrease in hemoglobin/hematocrit (up to 7%) occurred within hours of dosing but was asymptomatic.
- Antibody formation to serelaxin has occurred in 30% of subjects receiving serelaxin, but only after chronic s.c. administration. To date, the antibodies have been associated with no apparent adverse events. There is no evidence that the antibodies are neutralizing, nor is there evidence of any long-term sequelae.
- As with any protein, there is a possibility of hypersensitivity reactions, such as itching or skin rash, as well as the possibility of a potentially serious allergic reaction, which may result in hospitalization or even death. To date, no serious allergic reaction has been reported in the clinical studies.

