## **6 Visit schedule and assessments**

[Table 6-1](#) lists all of the assessments and indicates with an "X" the visits at which they will be performed (some of them apply only for part A or B or patients receiving serelaxin respectively).

Patients should be seen for all three visits on the designated day. However, falling outside this visit window will not constitute a protocol deviation. The investigator will bring the patient

back in for study visit as close as possible to recommended visit schedule. Documentation of attempts to contact the patient should be recorded in the patient's record.

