| Weight                                                                                                  | DS       | X   |                |                |                |                |                     |
| Vital signs (incl. blood pressure measurements)                                                         | DS       | X   | X              | X  | X  | X  | X                   |
| Local ECG                                                                                               | DS       | X   |                |                |                |                |                     |
| Fluoroscopic monitoring to ensure correct position of catheter (part B only)                            | S        |     | X              |                | X              |                |                     |
| Screening log                                                                                           | DS       | X   |                |                |                |                |                     |
| Pregnancy test                                                                              | DS       | X   | X              |                |                |                | X                   |
| Blood sample collection for hematology (central laboratory)                                             | DS       | X   |                |                |                |                |                     |
| Blood sample collection for clinical chemistry (central laboratory)                                     | DS       | X   |                |                |                |                | X                   |
| Heart rate monitoring                                                                       | -        |     | X              | X              | X              | X              |                     |
| Central ECG                                                                                             | DS       |     | X  | X  | X  | X  |                     |
| Randomization via treatment allocation cards (part A only)                                              | DS       |     | X              |                |                |                |                     |

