##### **6.5.5.1 Hematology**

Hemoglobin, hematocrit, red blood cell count, white blood cell count with differential, and platelet count will be measured.

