#### **Laboratory data**

##### **Part A (MRA)**

The summary of laboratory evaluations will be presented for two groups of laboratory tests (hematology and serum chemistry). Descriptive summary statistics for the change from baseline to each study visit will be presented. These descriptive summaries will be presented

by test group, laboratory test and treatment group. Change from baseline will only be summarized for subjects with both baseline and post baseline.

For each parameter, the maximum change from baseline within each study period will be analyzed analogously.

In addition, shift tables will be provided for all parameters to compare a subject's baseline laboratory evaluation relative to the visit's observed value. For the shift tables, the normal laboratory ranges will be used to evaluate whether a particular laboratory test value was normal, low, or high for each visit value relative to whether or not the baseline value was normal, low, or high. These summaries will be presented by laboratory test and treatment group. Shifts will be presented for most extreme values post-baseline.

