## 13 Appendix 1: Clinically notable laboratory values and vital signs

Clinically notable laboratory abnormalities for selected tests based on a percent change from baseline:

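### No hematology sample is scheduled after Visit 1, so the planned hematology change and shift tables have no scheduled data in either part

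*Protocol*

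**What the plan says.** Section 6 of the protocol makes Table 6-1 the complete list of assessments, with an X marking "the visits at which they will be performed". The two laboratory safety rows differ:

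- "Blood sample collection for hematology (central laboratory"): X at Visit 1 (Day -7) only.
- "Blood sample collection for clinical chemistry (central laboratory"): X at Visit 1 and at Visit 3, the column that also serves study drug discontinuation and premature withdrawal.

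Section 6.5.5.1 names the tests without a time point: "Hemoglobin, hematocrit, red blood cell count, white blood cell count with differential, and platelet count will be measured". Section 6.5.6 counts hematology among the general safety measures.

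The laboratory part of section 9.5.3 uses the same text for Part A and Part B: "The summary of laboratory evaluations will be presented for two groups of laboratory tests (hematology and serum chemistry"). It plans change from baseline to each visit, maximum change within each study period, and shift tables on the most extreme post-baseline value. It adds: "Change from baseline will only be summarized for subjects with both baseline and post baseline". Appendix 1 is headed "Clinically notable laboratory abnormalities for selected tests based on a percent change from baseline" and lists five hematology parameters: red cell count, haemoglobin, haematocrit, white cell count and platelets.

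Among the potential risks of serelaxin, section 3.6 states: "In CHF patients, a decrease in hemoglobin/hematocrit (up to 7%) occurred within hours of dosing but was asymptomatic".

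**The concern.** The schedule and the analysis text cannot both be followed as written. Section 9.5.3 and Appendix 1 presuppose a hematology value after dosing, and Table 6-1 provides none. A site that keeps exactly to the schedule delivers data from which no hematology change or shift table can be filled.

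Collecting information on safety and tolerability is a secondary objective in both parts (section 2.2). Section 3.6 says that serelaxin had not been studied in patients with cirrhosis and portal hypertension, and it names an early haemoglobin/haematocrit fall as a potential risk. The one hematology effect that the protocol places within hours of dosing has no scheduled measurement in that window. A reader who sees hematology listed as a safety measure in section 6.5.6 could take the absence of reported changes for reassurance, when nothing was looked for.

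**Working it through.** The protocol states no figure for this point, so there is none to reproduce. The check is a count of scheduled samples, set against the rule for entering the tables.

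**Inputs**

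- Planned patients (section 5.2): 40 in Part A, allocated 1:1, so 40 / 2 = 20 on serelaxin and 20 on terlipressin; 6 in Part B, all on serelaxin.
- Total planned: 40 + 6 = 46. On serelaxin: 20 + 6 = 26.
- Entry rule (section 9.5.3): change needs a baseline and a post-baseline value; shifts use the most extreme post-baseline value.

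**Scheduled samples per patient (Table 6-1)**

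| Row | Visit 1 | Visit 2, 0 min | Visit 2, 1-119 min | Visit 2, 120 min | Visit 2, recovery | Visit 3 / early stop | Post-baseline samples |
|---|---|---|---|---|---|---|---|
| Hematology | X | – | – | – | – | – | 0 |
| Clinical chemistry | X | – | – | – | – | X | 1 |

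**Could a sample be scheduled elsewhere?** No footnote to Table 6-1 adds one. The sample log in Appendix 4 covers only pharmacokinetic, immunogenicity and biomarker samples. The blank Visit 3 cell does not look like a fault in text extraction, because the chemistry row directly below keeps its Visit 3 mark.

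**Patients who can enter the tables from scheduled samples**

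- Hematology: 0 of 40 in Part A and 0 of 6 in Part B, so 0 of 46 overall and 0 of 26 on serelaxin. This holds for the change, maximum-change and shift outputs, and for the five hematology parameters in Appendix 1.
- Chemistry, for comparison: up to 46 of 46, through Visit 3.

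**Would a Visit 3 sample alone be enough?** It would fill the tables, but Visit 3 is on Day 29, about four weeks after the infusion. The fall in section 3.6 occurs within hours. Only a Visit 2 sample taken after the infusion has started falls in that window.

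**What can still be collected?** Amendment 1 states that Part A has completed enrollment and that 4 Part B patients have been randomized. Against a target of 6, 6 - 4 = 2 patients remain for a new Visit 2 sample, apart from replacements or an assigned patient not yet dosed. Any patient whose Visit 3 is pending could still give a Visit 3 sample; the protocol does not say how many that is.

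**The case against.** The best case for the plan is that this is a small exploratory study with one short infusion (expected maximum about 180 min in Part A and 130 min in Part B). Section 6.5.6 says that only general safety measures are used, with no specific additional ones. On that view hematology serves screening only, and section 9.5.3 carries generic laboratory text. No efficacy variable, sample size or eligibility rule depends on post-dose hematology, and an empty table does not mislead as a wrong number would.

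Much of this stands, and it limits the severity. It does not remove the contradiction. Section 6.5.6 itself lists hematology among the general measures. If screening-only sampling was intended, the change and shift outputs should not be promised. A separate analysis plan cannot resolve this, because it cannot supply samples that were not drawn.

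Three stronger readings are tempting, and the documents do not support them:

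- **That post-dose hematology can never become known.** Section 7.1 lets adverse events be detected through laboratory tests, so an unscheduled test could give an isolated value, and clinically evident anaemia would be reported as an adverse event. The accurate statement is that nothing is scheduled. Because the fall is described as asymptomatic, adverse event reporting is a weak substitute.
- **That added sampling would now give a usable estimate across all 26 serelaxin patients.** By Amendment 1 most of them can no longer give a new Visit 2 sample. The protocol also gives no within-patient haemoglobin variability from which to compute precision, and its 7% is an upper limit seen in heart failure patients, not an expected mean fall.
- **That the same fault explains every unusable entry in Appendix 1.** CPK, chloride and uric acid appear there but not in the section 6.5.5.2 panel. That is a separate, minor mismatch with its own cause and remedy.

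**Conclusion.** The point holds as a contradiction within the protocol. Table 6-1 schedules hematology once, before dosing, while section 9.5.3 and Appendix 1 require values after dosing. From scheduled samples, no planned patient can contribute to the hematology change, maximum-change or shift outputs, and the early haemoglobin/haematocrit fall listed in section 3.6 is not assessed.

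This rests on Table 6-1 being the governing schedule, as section 6 says, and on the planned numbers of 40 and 6. It needs no assumption about variability or effect size. The consequence is confined to one part of a secondary safety objective, and the primary analyses are untouched. It should be fixed before reporting.

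**What to change.** Reconcile Table 6-1 with section 9.5.3 and Appendix 1:

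1. **Patients not yet past the visit.** Add a hematology tube to blood draws already scheduled: the 120 min or end-of-recovery draw in serelaxin patients, and the Visit 3 chemistry draw in anyone with Visit 3 pending. The Visit 2 tube applies to about two Part B patients. A Visit 3 tube alone would not capture a fall within hours.
2. **All other patients.** Delete the hematology change, maximum-change and shift outputs and state in the report that post-dose hematology was not assessed. Mark the five hematology parameters in Appendix 1 accordingly. With so few new values, a listing by patient is more useful than a summary table.
3. **Separately**, align Appendix 1 with the section 6.5.5.2 panel for CPK, chloride and uric acid, by removing them from the one or adding them to the other.

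The cost is one extra tube at existing venepunctures for the few patients still to be seen, and an amendment to Table 6-1, section 9.5.3 and Appendix 1. For patients who have completed the study, the cost is wording only.

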## 6.1 Information to be collected on screening failures

Patients discontinuing prior to receiving study medication are considered screening failures. If a patient has withdrawn before entering the treatment phase, all Visit 1 eCRFs, including demographics, vital signs, portal hypertension and cirrhosis history, alcohol status, relevant medical history, and Screening Log entry with the primary reason for discontinuation should be completed. It is not necessary to complete all the required evaluations unless medically indicated.

## 6.2 Patient demographics/other baseline characteristics

Patient demographic and baseline characteristic data to be collected on all patients include: date of birth, age, sex, race, and ethnicity. Relevant medical history/current medical condition data includes data until the start of study drug. If possible, diagnoses and not symptoms will be recorded.

Demography/baseline characteristic information will be collected at Visit 1. All relevant medical history, portal hypertension and cirrhosis history and alcohol status will be collected at Visit 1 and reviewed at Visit 2 before administering any study drug.

## 6.3 Treatment exposure and compliance

All medications currently being taken, having been taken up to 30 days prior to entry into the study, and those taken after the start of study drug will be recorded on the Concomitant medications/Significant non-drug therapies eCRF.

Dosing information for study medication will be collected on corresponding dosage administration record eCRFs.

## 6.4 Efficacy

### 6.4.1 Part A: Blood flow measured via MRA

Haemodynamic data will be acquired using a 3.0 Tesla whole body Siemens Verio dedicated research MR scanner. A non-contrast MR angiography sequence (Siemens NATIVE TrueFISP (True Fast Imaging with Steady state Precession)) will be performed to acquire phase contrast blood flow measurements from vessels of interest (right and left renal artery, hepatic artery, superior mesenteric artery, descending thoracic aorta, portal vein, descending

abdominal aorta, and azygos vein). For each vessel the velocity encoding of the acquisition will be adjusted on a patient-by-patient basis.

Scan sequences will be performed pre and post 120 minutes of serelaxin infusion or terlipressin acetate bolus administration. During scanning, all images will be checked visually after each flow measurement sequence; if motion artefacts are detected, the individual vessel scan will be repeated. Flow measurements will be derived from analysis of the phase contrast images using the Siemens Argus Flow software directly on the scanner workstation console. The total acquisition time for each MRA sequence is approximately 45-60 minutes (incl. repeats in case of motion artefacts).

On the vascular images where the phase contrast sequence has been applied for assessment of flow rates (hepatic artery, portal vein, superior mesenteric artery, descending thoracic aorta (acquired 2 cm above the coeliac trunk), inferior aorta (acquired 2 cm above the iliac bifurcation), renal arteries, azygos vein)), contours are drawn manually (or semi-automatically after seed points are indicated at the lumen boundary) at end-diastole (first image of the cine acquisition) and end-systole (smallest cavity size during cardiac cycle) on every slice. For the flow measurements, the lumen of each vessel will be carefully evaluated at the peak systolic phase image, and the area of the lumen will be used as the region of interest for the flow and velocity quantification program, yielding values that represent average volumetric flow rate and peak systolic velocity within the vessel ([Barthelmes et al 2009](#)).

For detailed instructions on MRA procedure, please refer to the MRI manual that will be provided separately.

#### **6.4.2 Part B: Direct venous pressure measurement**

Patients with cirrhosis and a TIPSS *in situ* will undergo portography at the time of routine shunt assessment at the site's X-ray department. Typically, an introducer sheath is inserted under local anaesthetic into the right internal jugular vein and a catheter inserted to measure inferior vena cava pressure (IVCP) and right atrial pressure (RAP) using fluoroscopic guidance. After catheterization of the TIPSS, shunt patency is determined by injection of iodinated contrast medium, followed by measurement of portal vein pressure (PVP) and calculation of the portal pressure gradient (PPG). A non-study specific informed consent form will be signed by the patients according to the site's standard practice for their portography procedure as performed for routine TIPSS assessment. After portography has confirmed a fully functioning shunt without variceal filling, and a PPG of >5mm Hg, the PV catheter will be secured in position and the patient transferred to the site's Clinical Research Facility. Fluoroscopic monitoring will be used to confirm that the catheter is still properly positioned in the PV and did not move during the transfer. The catheter position will be corrected if needed. Just prior to starting the serelaxin study drug infusion the pre-dosing PVP as measured at the site's X-ray department will be confirmed. The catheter will be kept in the PV, secured in place and not moved throughout the measurement period of 2 hours during which the PVP will be measured at 15 min intervals (i.e. prior to and at 15, 30, 45, 60, 75, 90, 105 and 120 min of serelaxin infusion). Before complete withdrawal of the catheter, a second IVCP and RAP reading will be obtained under fluoroscopic guidance.

### 6.4.3 Appropriateness of efficacy assessments

PHT is the earliest and most important consequence of cirrhosis and underlies most of the clinical complications of the disease. Indirect measurement of PHT by the hepatic venous pressure gradient (HVPG) is the gold standard method for evaluating the presence and severity of PHT, but this technique is considered invasive and is not routinely performed in all centers. A reduction in HVPG (e.g. after drug therapy) below 12 mmHg or by >20% from baseline is associated with a significant reduction in complications and death ([Ripoll 2007](#)). Although a novel therapy for PHT would ultimately need to demonstrate efficacy in terms of HVPG reduction, one could argue that this approach is both too invasive and too restrictive for exploratory studies. HVPG captures only limited information with no indication of the relative influence of a drug on the various factors that affect PHT including hepatic vascular resistance (due to scar tissue and intrahepatic vasoconstriction) and extrahepatic haemodynamic abnormalities involving both the splanchnic and systemic circulations. Accordingly, we propose a unique strategy using complementary but distinct approaches to provide a comprehensive assessment of the haemodynamic response to serelexin in patients with cirrhosis and PHT.

#### Magnetic resonance angiography

MRA is a reliable technique for the non-invasive assessment of blood flow changes in the body. MRA has previously been used to successfully investigate splanchnic blood flow ([Barthelmes et al 2009](#)) and present research efforts are focused on application of the MRA assessment to evaluate the 'splanchnic steal' phenomenon in patients with cirrhosis ([McAvoy 2010](#)). Through assessment of azygos flow, MRA also has been shown to accurately stage varices in patients with cirrhosis ([Gouya et al 2011](#)).

Using MRA, the effects of serelexin on the hepatic, splanchnic, renal and systemic circulations will be evaluated. Taken together, these measurements will establish the potential for serelexin as a therapy in cirrhosis (e.g. to reduce PHT in variceal bleeding and/or to increase renal blood flow in hepatorenal syndrome). Furthermore, as the approach utilizes a state of the art MR platform and an optimized non-contrast sequence, the risk of the MRI for study participants is an absolute minimum.

#### Direct venous pressure measurement

Although MRA enables a broad assessment of blood flow changes, it does not directly measure pressure. The HVPG is a good reflection of portal pressure in patients with alcoholic or viral cirrhosis, but it remains an invasive procedure. Furthermore, after the acute administration of a drug acting on the splanchnic circulation, the HVPG measurement does not necessarily provide a reliable estimation of the magnitude of the changes in the portal pressure ([Valla et al 1984](#)). Direct portal vein pressure measurement in patients with a TIPSS has been found to be reproducible with a coefficient of variation of <10% ([Forrest et al 1996](#)). Although the presence of a shunt alters intrahepatic haemodynamics by removing a large element of mechanical resistance, a significant dynamic resistive component remains. Patients with a TIPSS *in situ* undergo regular shunt assessment for patency and portal pressure monitoring as part of standard medical care. TIPSS therefore provides a valuable opportunity

to directly assess changes in portal pressure in patients with cirrhosis at the time of portal vein catheterization for routine portography.

